## Abstract

**Introduction:**

Vaccines have emerged as the most effective tool in the fight against COVID-19. Governments all over the world have rolled out the COVID-19 vaccine program for their populations. Oxford-AstraZeneca COVID-19 vaccine (COVISHIELD™) is widely used in India. A large number of Indian people have been consuming various traditional medicines in the hope of better protection against COVID-19 infection. Several studies have reported immunological benefits of *Withania somnifera* (Ashwagandha) and its potential as a vaccine adjuvant. We propose to study the safety, immunogenicity and clinical protection offered by a 6-month regimen of Ashwagandha in participants who volunteer to be vaccinated against COVID-19 (COVISHIELD^TM^) in the ongoing national program of vaccination.

**Methods and Analysis:**

We designed a prospective, randomized, double-blind, parallel-group, placebo-controlled, two-arm, exploratory study on healthy volunteers receiving the COVISHIELD^TM^ vaccine. The administration of Ashwagandha will begin within 7 days of the first or second dose of COVISHIELDTM. Primary outcome measure is immunogenicity as measured by SARS-CoV-2 spike (S1) and RBD-specific IgG antibody titres. Secondary outcome measures are safety, protective immune response and quality of life measures. All adverse events will be monitored at each time throughout the study. Participants will be tracked on a daily basis with a user-friendly mobile phone application. Following power calculation 600 participants will be recruited per arm to demonstrate superiority by a margin of 7% with 80% power. Study duration is 28 weeks with interim analysis at the end of 12 weeks.

**Ethics and Dissemination:**

Ethics approval was obtained through the Central and Institutional Ethics Committees. Participant recruitment commenced in December 2021. Results will be presented in conferences and published in preprints followed by peer-reviewed medical journals.

**Clinical Trial Registration:**

[www.ClinicalTrials.gov], identifier [CTRI/2021/06/034496].

## Introduction

Vaccines have emerged as the most effective tool in the fight against COVID-19. Governments all over the world have rolled out COVID-19 vaccine program for their populations. Clinical studies on vaccine efficacy suggest a role of high neutralizing antibody titers, robust CD8+ and Th1-biased CD4+ responses in protection against SARS-CoV-2 infection and also break through infections (1–4). With the emergence of new variants of concern, persistence of vaccine induced humoral and cell mediated immune response is being considered as key to fight against pandemic. There is ongoing global research on further enhancing the effectiveness of existing vaccines either by developing new vaccines against variants or by booster vaccination (5).

Botanical immunomodulators especially those based on traditional medicine offer opportunities for combined use with vaccines to induce optimum and persistent host immune responses (6). *Withania somnifera* (WS) also known as Ashwagandha in Ayurveda is a widely used medicinal plant for its immunomodulatory properties. Various studies on Ashwagandha have established its use as an immune-adjuvant in infection, inflammation and diseases such as arthritis and cancer (7). Immunoadjuvant activity of Ashwagandha has been reported in an infection model when co-administered with DPT (diptheria, pertussis, tetanus) vaccine (8). The long-term safety of Ashwagandha is well documented (9–13). It is also being investigated in comparison with hydroxychloroquine in a randomized controlled multi-centric clinical study for its prophylactic activity against COVID-19 in high-risk health care workers (CTRI/2020/08/027163, CTRI/2020/05/025332).

Based on our earlier studies, we hypothesize that co-administration of Ashwagandha with COVID-19 vaccine may result in better safety, immunogenicity and protection. Further, the vaccine efficacy, 22–90 days after a single dose of ChAdOx1 has been reported to be 76% (14). In this context it would be interesting to investigate whether Ashwagandha co-administration is able to provide a better immune response particularly after the first dose of the vaccine.

The primary hypothesis is that a long-term administration of Ashwagandha along with COVISHIELD^TM^ vaccine leads to a better protection against COVID-19 in healthy populations as compared to COVISHIELD^TM^ vaccine alone in terms of augmented immune-response, reduced incidence of breakthrough SARS-CoV-2 infections, good safety and tolerance.

We therefore propose to study the effect of Ashwagandha administration in participants vaccinated against COVID-19 vaccine (COVISHIELD^TM^) on safety, immunogenicity and protection in healthy population. COVISHIELD^TM^ consists of a replication-deficient chimpanzee adenoviral vector ChAdOx1, containing the SARS-CoV-2 structural surface glycoprotein antigen (spike protein; nCoV-19) gene (15, 16). Safety will be assessed by measuring the occurrence of adverse events. Immunogenicity will be assessed by measuring the SARS-CoV-2 S1 and RBD-specific IgG titers. Protective immune response will be evaluated by measuring SARS-CoV-2 specific (B1.617.2 and USA-WA1/2020 variants) neutralizing antibody titers; percent seroconversion after each vaccine dose; number of participants with SARS-CoV-2 breakthrough infections. An important aim of the study is also to evaluate the salubrious effects of Ashwagandha on physical and mental health and quality of life. Considering that long-term immune response to the vaccine will have implications for prevention of reinfection, it is also of interest to study the effect of Ashwagandha on the sustenance of the vaccine response. An auxiliary protocol is also planned to study the effect of Ashwagandha on T cell responses in vaccinated individuals. This study will help to understand the potential of Ashwagandha to improve vaccine response on a long-term basis.

## Methods and Analysis

### Patient and Public Involvement

This protocol was developed to address the immediate need to study safety and immunogenicity of Covid-19 vaccine among participants who orally consumed immunomodulating agents concurrently. Patients were not involved in the design, recruitment or conduct of the study. Results of the study will be disseminated to public after peer-review journal publication.

### Study Design

This will be a prospective, randomized, double blind, parallel group, placebo controlled, multi-centric study on healthy volunteers receiving the COVISHIELD^TM^ vaccine with a superiority design. The trial will be conducted at multiple locations as shown in the CTRI. Consenting and eligible volunteers will be enrolled and randomized to either of the two study arms (Ashwagandha plus COVISHEILD^TM^ vaccine or placebo plus COVISHIELD^TM^ vaccine) as per the protocol. The participants will be jointly evaluated by an Ayurvedic and a modern medicine physician for several clinical and laboratory measures. An Ayurveda based clinical assessment will also be carried out. The various assessments to be carried out are shown in Tables 1, 2.

**Table 1 T1:** Clinical assessment schedule.

**Visit**	**Visit 0 Screening (Day −7 to −1)**	**Visit 1** **Enrollment and randomization (Day 1)**	**Visit 2 (4 wks)**	**Visit 3:(8 wks)**	**Visit 4 (12 wks)**		**Visit 5:(16 wks)**	**Visit 6** **Intervention completion1** **(24 wks)**	**Visit 7: Study completion (28 wks)**
Informed consent	X					**Interim analysis**			
Demographics	X								
Inclusion exclusion criteria	X								
Medical history	X								
Concomitant illness	X		X	X	X		X	X	X
Randomization		X							
Complete physical examination	X	X	X	X	X		X	X	X
WHO QOL BREF^@^		X			X			X	X
HR-BHF^#^		X			X			X	X
Vital signs	X	X	X	X	X		X	X	X
Ayurvedic evaluation: prakriti		X							
Ayurvedic evaluation: dhatu sarata		X	X	X	X		X	X	X
Ayurvedic evaluation:		X	X	X	X		X	X	X
Electrocardiogram	X							X	
Chest radiograph	X							X	
Study drug dispensation		X	X	X	X		X		
Adverse event assessment			X	X	X		X	X	X
Mobile App–Kavach–self reported questionnaire*		X	X	X	X		X	X	X
Completion and outcome report									X

* *To be completed daily by participants*.

# *HR-BHF: Health Related-Habits, Behavior and Fitness*.

@ *WHO QOL BREF: World Health Organization Quality of Life Instruments-short form*.

**Table 2 T2:** Schedule of laboratory investigations.

**Visit**	**Visit 0 Screening (Day −7 to −1)**	**Visit 1 Enrollment and randomization (Day 1)**	**Visit 2 (4 wks)**	**Visit 3: (8 wks)**	**Visit 4 (12 wks)**	**Interim analysis**	**Visit 5:(16 wks)**	**Visit 6** **Intervention completion** **(24 wks)**	**Visit 7: Part 1 completion (28 wks)**
CBC: blood hemoglobin, total and differential count, platelets Erythrocyte sedimentation rate (Westergren)	X				X			X	
D-dimer	X				X			X	
LFT: serum liver enzymes-SGOT, SGPT, alkaline phosphatase Serum albumin, globulin, bilirubin	X				X			X	
RFT: blood urea nitrogen Serum creatinine	X				X			X	
Blood sugar profile (BSL fasting and HbA1c)	X				X			X	
Urine routine	X				X			X	
^+^Urine pregnancy test	X		X	X	X		X	X	X
^#^RT-PCR throat/nose swab testing for SARS-CoV2 RNA	X		X	X	X		X	X	X
SARS- CoV-2 S1, RBD and N Specific IgG		X	X	X	X		X	X	X
sVNT					X			X	X
SNT (Wuhan isolate USA-WA1/2020 and Delta variant B1.617.2)					X				X

# *RT-PCR throat nose swab test will be repeated in participants in case of development of any symptoms during the study duration*.

+ *for female participants*.

*Additional studies on measurement of secretory IgA and T cell responses are planned on a subset of the participants*.

If the vaccinated individual (after first or second dose) contracts COVID 19, then he/she shall be withdrawn from the study and will be treated under the supervision of COVID-19 physician till recovery. The participants who are withdrawn prematurely will be encouraged to continue follow up in a separate group as per the discretion and supervision of the study physician. The latter group will be permitted to use the current protocol methods and analyzed separately. All participants will be monitored for safety, immune response and occurrence of any breakthrough SARS-CoV-2 infection. An interim analysis at the end of 12 week is planned to evaluate the effect of Ashwagandha co-administration on safety and immune response following the first dose of the vaccine. The final analysis of data will be carried out after all the participants have completed the study at the end of 28 weeks.

### Recruitment, Screening, Consent

Apparently healthy volunteers (18–45 years) who have received either the first or second dose of the COVID-19 vaccine as part of the Government of India vaccination programme will be included in this study. The study will include up to 300 participants who have received the first dose and at least 900 participants who have received the second dose. The investigator will be responsible for obtaining written informed consent from each participant prior to screening as per the national ethics guidelines (17). An information sheet in language best understood by the participant, giving details of the study will be provided to the participant for study and discussion if any with the investigator. Enough time will be given to the participant to make a voluntary decision to participate. Participant will be encouraged to ask questions and clear all doubts in a face to face interview with the investigator. After fully satisfying with the various provisions of the research study the participant will be asked to sign the consent form. Participants will be screened comprehensively by the study physicians for eligibility and to exclude any contraindication to participation in the study. If found eligible, participants will be randomized and enrolled. Participants will be followed up at predetermined time endpoints (eight visits including screening and completion visits) as per protocol till study completion (week 28).

### Eligibility

#### Inclusion Criteria

Apparently healthy adults of either sex aged 18–45 years who have received either the first or second dose of COVID-19 vaccine; SARS-COV-2 RT-PCR negative volunteers; Written informed consent by the participants; Willing to comply with study protocol requirements; Female participants of childbearing potential with a negative urine pregnancy test.

#### Exclusion Criteria

Any known co-morbidity or acute illness with or without symptoms at the discretion of the investigator; History of known hypersensitivity to any component of the study material (Ashwagandha); Any confirmed or suspected condition with impaired/altered function of the immune system or conferring a possible risk suggested by investigations (e.g., increased levels of D-dimer); Women who are breast-feeding and pregnant; Individuals who are using any intervention (AYUSH or otherwise) for prophylaxis or for immune boosting or that may influence immune system e.g., steroids, methotrexate, anti-rheumatoid agents, drugs from AYUSH systems within 30 days prior to screening; Individuals who have received systemic immunoglobulins or blood products within 3 months prior to screening.

#### Withdrawal Criteria

The participants with drug compliance <70% (estimated by recorded tablet consumption), any serious adverse event, or those with positive RT-PCR tests, or clinical symptoms of COVID-19 will be withdrawn from the study. Withdrawn participants who are RT-PCR positive will be referred to a COVID-19 treatment facility for standard care.

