##### Secondary Outcome Measures

Safety as measured by occurrence of adverse events. Protective immune response as measured by SARS-CoV-2 specific neutralizing antibody titer; Duration of sustenance of SARS-CoV-2 virus neutralizing antibody titer; percent seroconversion after each vaccine dose; number of participants with SARS-CoV-2 breakthrough infections; proportion of participants with COVID 19 (RT PCR assay confirmed) after the first dose and both showing evidence of infection before vaccination (Time frame: Day 1 vaccination to Week 12 or second dose and whichever is earlier); proportion of participants with COVID-19 (RT-PCR assay confirmed) after completion of the second dose (Time frame: Second dose to week 28 or study completion) and Quality of life measured using standard WHO Quality Of Life-BREF 1997 (20) and recently designed and validated Health Related-Behavior Habit Fitness (CRD Pune version 2020) questionnaires. All clinical and laboratory investigations and assessments pertaining to general health, and to rule out concurrent medical illness including COVID-19 will be carried out as per Tables 1, 2.

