#### Analysis

A standard statistical software package will be used for statistical tests (parametric and non-parametric). The analysis will be both intention-to-treat (ITT) and as per-protocol (PP). All randomized participants will be included in the safety analysis. All statistical processing will be performed using standard statistical package (SPSS, BMDP, and CIA) unless otherwise stated. The data will be individually analyzed for central tendencies (mean, median), range, standard deviation and 95% confidence intervals for each intervention arm in the study. Titer data will be “log” transformed before any analyses [and GMT, GSD, etc. will be reported and will be used for testing with respect to that parameter. Data will be tabulated and graphically shown using standard format using MS Excel and other software programs. Standard parametric (Student *t*-tests–paired and unpaired, ANOVA, etc.) and non-parametric statistical tests (Wilcoxon Signed Rank test, Mann-Whitney “U” test, Kruskal-Wallis test, etc.) will be used depending upon the normality of the data, level of measurement and appropriateness/applicability. Fisher's exact test or Chi square will be used to test the proportion of participants classified as efficacy failures and those with AE. All AEs will be presented as proportion and with Wilson's recommended exact binomial 95% Confidence Interval.

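### Participants are withdrawn from the study, not only from tablets, on triggers that arise after randomisation; this conflicts with the promised intention-to-treat analysis and with infection follow-up to week 28

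*Protocol article*

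**What the plan says.** The Protocol article deals with withdrawal in two places.

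- **Withdrawal Criteria** lists four triggers. The first two are "The participants with drug compliance <70% (estimated by recorded tablet consumption), any serious adverse event"; the others are "those with positive RT-PCR tests, or clinical symptoms of COVID-19 will be withdrawn from the study". The withdrawal is from the study, not merely from the tablets.
- **Study Design** (the paragraph after Table 2) says that a vaccinated participant who "contracts COVID 19, then he/she shall be withdrawn from the study". People withdrawn prematurely are to be "encouraged to continue follow up in a separate group as per the discretion and supervision of the study physician". It continues: "The latter group will be permitted to use the current protocol methods and analyzed separately".

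Four other statements bear on this.

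- **Analysis**: "The analysis will be both intention-to-treat (ITT) and as per-protocol (PP". The same section commits all randomised participants to the safety analysis, but makes no such statement for efficacy.
- **Primary Outcome Measure and Table 2**: S1 and RBD IgG titres, drawn on Day 1 and at weeks 4, 8, 12, 16, 24 and 28.
- **Secondary Outcome Measures**: "number of participants with SARS-CoV-2 breakthrough infections", together with two proportions of RT-PCR-confirmed COVID-19. One of these has a window from the second dose to week 28 or study completion.
- **Table 2 footnote**: "RT-PCR throat nose swab test will be repeated in participants in case of development of any symptoms during the study duration". Study Design adds that all participants are monitored for breakthrough infection.

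**The concern.** Each trigger is a post-randomisation event that the tablet could influence: adherence and serious adverse events through tolerability, infection and symptoms through the protection that the trial hopes to show. If people leave on these triggers and any later data sit in a separate group, the arms being compared are no longer the arms that were randomised. Removing low compliers is how a per-protocol set is built. Doing it through study withdrawal removes much of the contrast between the two analyses that the plan promises.

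Two outcomes are exposed. The titre comparison loses later samples from a selected group. The infection comparison loses events and time at risk among those who leave without a positive test. Data not collected after withdrawal cannot be recovered by any later definition of ITT.

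**Working it through.** **1. Which data are lost, by trigger**

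| Trigger | Later IgG titres | First infection | Safety |
|---|---|---|---|
| Positive RT-PCR | Lost, or in the separate group | Counted: the positive test is the event | Covered |
| Symptoms, RT-PCR negative | Lost, or voluntary only | Missed if it occurs later | Covered |
| Compliance <70% | Lost, or voluntary only | Missed if it occurs later | Covered |
| Serious adverse event | Lost, or voluntary only | Missed if it occurs later | Covered |

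The safety column rests on Analysis (all randomised participants) and Adverse Events (safety assessed in all withdrawals).

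**2. Statements that do not fit together**

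- The Withdrawal Criteria end participation on symptoms alone. The Table 2 footnote calls for an RT-PCR on symptoms, and both infection proportions in Secondary Outcome Measures need RT-PCR confirmation.
- Study Design says all participants are monitored for breakthrough infection, and one outcome window runs to week 28. Withdrawal before week 28 with only voluntary follow-up does not secure either.
- Analysis promises ITT. Study Design takes a post-randomisation subgroup out of the comparison.

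**3. Scale of selection bias (illustration only)**

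The documents give no withdrawal rate and no response rate among the withdrawn. Assume no true effect, an 80% response in both arms (borrowed from the 80% that Sample Size and Power gives as vaccine efficacy), a withdrawn share w, and response r among the withdrawn. The rate in the retained set is (0.80 − w·r)/(1 − w).

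| r | w in each arm | Retained rates | Spurious difference |
|---|---|---|---|
| 60% | 10% v 10% | 82.2% v 82.2% | 0 |
| 60% | 10% v 20% | 82.2% v 85.0% | 2.8 points |
| 60% | 10% v 30% | 82.2% v 88.6% | 6.3 points |
| 40% | 10% v 20% | 84.4% v 90.0% | 5.6 points |

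For example, (0.80 − 0.20×0.60)/0.80 = 0.85. The plan's target difference is 7%. In this illustration equal withdrawal gives no bias, and the arm that loses more low responders looks better.

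**4. Missed infections (illustration only)**

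If a share w leaves evenly over follow-up for reasons unrelated to infection, and infections are evenly spread, about w/2 of them go unseen. With 60 expected in 600 (an assumed 10% risk) and w = 20%, the count is 60 × (1 − 0.20/2) = 54.

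**5. Power**

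Inputs from Sample Size and Power: 80%, a 7% margin (read as 80% v 87%), 80% power, and alpha 2.96%, which is stated for the interim. Overall alpha and sidedness are not given. The two-sided pooled formula is n = [z₁₋α/₂√(2p̄(1−p̄)) + 0.842√(p₁(1−p₁)+p₂(1−p₂))]²/0.07², with p̄ = 0.835.

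- Alpha 0.05 (z = 1.960): 441 per arm.
- Alpha 0.0296 (z = 2.175): 511 per arm.

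Unpooled variance gives 438 and 508. None of these reproduces the 600 per arm, which the plan describes as rounded. All lie below it, so 600 leaves room for losses of 1 − 441/600 = 26.5% or 1 − 511/600 = 14.8% before power falls under 80%.

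**The case against.** **Infection count.** A reader might infer that the rule censors the breakthrough outcome altogether. It does not. The outcome counts participants, a first positive RT-PCR is itself the event, and symptoms prompt a test. The loss is confined to those who leave without a positive test, and to later-window and titre data from those infected earlier.

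**Reach of the separate analysis.** That sentence comes in the paragraph on contracting COVID-19. Its wording refers to premature withdrawals in general, but the Withdrawal Criteria attach no analysis rule to low compliance or serious adverse events. It is therefore not established that all four groups are analysed separately. What stands is that all four leave the study and that nothing secures their follow-up.

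**Titres after infection.** Natural infection can itself raise S1 and RBD IgG, so setting aside later samples in the main titre analysis is defensible. That is a reason to state a rule for those samples, not to end follow-up. Nothing in the text says that samples taken before infection are discarded.

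**Size.** A reader might want a definite attenuation of the titre difference. If every infected person is deleted, and one assumes a true effect of 0.08 log10, an SD of 0.5, placebo infection risk of 5–30% and an infection odds ratio of 0.1 or 0.3 per log10 of titre, attenuation runs from about 2% to 16%. Every one of those inputs lies outside the documents, and deleting all samples from infected people is not what the plan says. The figure cannot be relied on.

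**Power.** A reader might also infer that the trial is underpowered. The 600 per arm exceeds every requirement computed above, and an unstated dropout allowance in an article is no defect.

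**Detail left to a full plan.** The handling of withdrawals within ITT may well be set out elsewhere. But withdrawal from the study is a conduct rule stated here, and no analysis plan can supply samples that were never drawn.

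**Conclusion.** The point holds in a limited form. The Withdrawal Criteria and Study Design take randomised participants out of the study on post-randomisation triggers that may depend on treatment, with only voluntary follow-up afterwards and a separate analysis at least for the premature withdrawals that Study Design describes. This conflicts with the ITT commitment in Analysis, with the statement that all participants are monitored, and with the infection window to week 28.

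The main harm is possible bias in the titre comparison, with incomplete infection counts after withdrawal without a positive test. Its direction and size depend on how many leave each arm and how they differ from those who stay, and the documents give neither. The illustrations show only that the effect can be nil when withdrawal is balanced and can approach the plan's 7-point target when it is not. First RT-PCR-positive infections and the safety analysis are not affected. Recruitment began in December 2021, so visits missed under the present rule are a permanent loss.

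**What to change.** Reconcile Withdrawal Criteria, Study Design, Secondary Outcome Measures and Analysis as follows.

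- Leave the rules on stopping tablets and on COVID-19 care as they are, but separate stopping tablets from leaving the study.
- Keep every randomised participant in the scheduled visits, RT-PCR and antibody sampling to week 28 unless consent is withdrawn.
- Define ITT as all randomised participants by allocated arm, and remove the separate-analysis provision for that analysis.
- Use compliance below 70% only to define the per-protocol set.
- Do not end follow-up on symptoms without RT-PCR confirmation.
- State how titres after confirmed infection are handled in the main analysis, with a sensitivity analysis that includes them.

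The cost is a protocol amendment with matching analysis wording, and some extra visits and samples from people no longer taking tablets. The visit schedule itself does not change.
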